# Comparative study of the effect of neuromuscular electrical stimulation and oral administration of branched-chain amino acid on preventing sarcopenia in patients after living-donor liver transplantation: study protocol for an open-label randomized controlled trial

**DOI:** 10.1186/s13063-021-05086-y

**Published:** 2021-02-12

**Keywords:** Branched-chain amino acids, Decompensated cirrhosis, Living donor liver transplantation, Neuromuscular electrical stimulation, Sarcopenia

## Abstract

**Background:**

Liver cirrhosis is the irreversible fibrosis of the liver and causes refractory ascites and hepatic encephalopathy, which might not respond to treatment. Living donor liver transplantation (LDLT) is an effective treatment for patients with cirrhosis. However, post-LDLT patients are prone to muscle atrophy and sarcopenia. Therefore, physiotherapy of post-LDLT patients is essential for preventing the progression of sarcopenia. Recently, rehabilitation using neuromuscular electrical stimulation (NMES) has been reported to be useful for preventing the progression of sarcopenia. Similarly, nutrition therapy is essential for post-LDLT patients because these patients frequently experience malnutrition. However, the effects of combined NMES and nutrition therapy on post-LDLT patients remain unknown.

**Methods/design:**

This open-label, randomized, parallel-group study will compare the effects of combined therapy with NMES and branched-chain amino acids (BCAA) with those of NMES alone in patients with decompensated cirrhosis after LDLT. After LDLT, 50 patients with decompensated cirrhosis will be randomly assigned to receive NMES with BCAA or NMES without BCAA. The duration of the intervention will be 3 months. To analyze the change in skeletal muscle mass, InBody 770 body composition and body water analysis and ultrasonography will be performed before LDLT and 4 weeks and 12 weeks post-LDLT. The primary endpoint is changes in the skeletal muscle mass from baseline to 3 months. Important secondary endpoints are the changes in the skeletal muscle mass from baseline to 1 month and changes in the quadriceps strength from baseline to 1 month.

**Discussion:**

The results of this study are expected to provide evidence regarding the effect of NMES combined with BCAA therapy on the skeletal muscle of post-LDLT patients.

**Trial registration:**

Japan Registry of Clinical Research jRCTs071190051. Registered on February 26, 2020.

## Background

Liver cirrhosis is the irreversible fibrosis of the liver; it has various causes and is classified into compensated cirrhosis and decompensated cirrhosis [1]. Patients with decompensated cirrhosis often experience complicating refractory ascites and hepatic encephalopathy, which might not respond to systemic treatment [2, 3]. Living donor liver transplantation (LDLT) is an effective treatment for patients with decompensated cirrhosis. However, such patients often develop muscle atrophy and sarcopenia, leading to decreased quality of life [4–6]. Exacerbation of sarcopenia affects the prognosis of patients with cirrhosis [7]. Moreover, after LDLT, there are many factors that limit post-operative weaning, such as an unstable fluid balance due to decreased hepatic metabolism and associated retention of pleural effusion and ascites [8], which lead to muscle atrophy and sarcopenia.

Physical therapy is considered essential post-LDLT to facilitate motor function recovery [9–11]. Additionally, physical performance potentially increases with the recovery of liver function [12]. Since recovery after transplantation differs markedly across patients, no specific protocols have been established for postoperative physical therapy.

Recently, rehabilitation using neuromuscular electrical stimulation (NMES) has been reported to be useful for preventing the decline in the activities of daily living (ADLs) [13]. NMES is a practical, passive therapy that can be safely applied to maintain quadriceps muscle mass in seriously ill patients [14]. We have previously reported that NMES, combined with conventional physical therapy, significantly improved muscle mass in post-LDLT patients, compared with physical therapy alone [15].

Furthermore, after LDLT, patients are frequently malnourished. Hence, nutrition therapy, as well as rehabilitation, is essential after LDLT. A previous report indicated that nutritional status and metabolism were improved by adding branched-chain amino acids (BCAA) for 4 weeks after LDLT [16]. However, the effects of a combination of BCAA and NMES on patients after LDLT remain unknown. Therefore, there is a need to evaluate the effects of postoperative adjuvant therapies, such as physical therapy and nutritional therapy, on preventing the decline in ADLs due to muscle atrophy or exacerbation of sarcopenia after LDLT in patients with decompensated cirrhosis.

This study will aim to determine whether NMES and BCAA combination therapy can contribute to the recovery of skeletal muscle mass in patients with decompensated cirrhosis after LDLT.

## Methods/design

### Study design

This is a pilot trial to assess the effect of NMES and BCAA combination therapy on skeletal muscle mass. We have designed a single-center, randomized, open-label, parallel-group, active-controlled trial for patients with decompensated cirrhosis scheduled to undergo LDLT. We will randomly assign 50 patients, in a 1:1 ratio, to the NMES and BCAA group or the control group (receiving treatment with NMES only). The overall objective is to test for the superiority of the NMES and BCAA group compared with the control group. The study follow-up duration will be 3 months. The study will be conducted at Nagasaki University Hospital, Japan, and the study design is summarized in Fig. 1.

**Fig. 1 Fig1:**
[figure not shown]
Study design. An eligibility check is conducted, and the patient’s informed consent is obtained at visit 1. The patients who satisfy the inclusion criteria are enrolled in the study at visit 2; they are randomized in a 1:1 ratio to the NMES and BCAA group (administered Aminoleban EN 100 mg) and the control group. BCAA, branched-chain amino acids; LDLT, living donor liver transplantation; NMES, .neuromuscular electrical stimulation

### Outcomes

The primary outcome measures are changes in the skeletal muscle mass, as determined using the InBody 770 (InBody, Tokyo, Japan). For this parameter, any change will be determined based on the difference between the measurement results at baseline (day 0) and 3 months post-LDLT.

The study’s secondary outcome measures are as follows: changes in the skeletal muscle mass from baseline to 1 month post-LDLT; changes in the Skeletal Muscle Index (SMI), as determined by the InBody 770; changes in quadriceps muscle thickness, as determined by real-time B-mode ultrasonography (ProSound 2; Hitachi-Aloka Medical Co., Tokyo, Japan); quadriceps strength, as determined by a handheld dynamometer fixed with a belt (μ-Tas F^−1^; Anima Corporation, Tokyo, Japan); and handgrip strength from baseline (day 0) to 1 month and 3 months post-LDLT.

### Sample size estimation

This is a trial to assess the changes in skeletal muscle mass by NMES and BCAA combination therapy as compared with NMES only. There is no prior similar study that can be used to estimate the precise optimal sample size. We estimated sample size with reference to a study published by Koya et al. in 2017 [17]. This was a retrospective study comparing the skeletal muscle mass before and after transarterial chemoembolization (TACE) in 54 hepatocellular carcinoma patients who were rehabilitated for 1 week after TACE; the study reported that the presence or absence of BCAA affected changes in muscle mass. We set the number of cases based on the average and the variance-covariance matrix of the SMM value, before and after treatment in the BCAA group and the non-BCAA group, obtained from this study. The justification for this sample size is based on the rationale concerning feasibility and precision regarding the mean and variance of the primary outcome measures.

### Patients and public involvement statement

There is no patient or public involvement in this trial.

### Participants and recruitment

Fifty participants aged ≥ 20 years will be recruited into the study. The enrollment started in February 2020. All participants have been diagnosed with decompensated liver cirrhosis and will undergo LDLT. Patients who fulfill the inclusion criteria described below will be invited for eligibility screening. The transplant coordinator informs investigators of the patients scheduled for LDLT. The principal investigator and co-investigators recruit the participants among these patients and obtain written informed consent from the participants. The principal investigator is responsible for obtaining informed consent, and there are no additional consent provisions for the collection and use of participant data and biological specimens in ancillary studies. The recruitment rate and the consent rate will be evaluated at the end of the study.

### Inclusion criteria

As shown in Fig. 1, participants must fulfill the following criteria to be eligible for inclusion at their first visit to Nagasaki University Hospital (visit 1): (*1*) aged ≥ 20 years, (*2*) either sex, (*3*) diagnosis of decompensated liver cirrhosis, (*4*) Performance Status (ECOG PS) of 0–2, and (*5*) written informed consent provided.

### Exclusion criteria

Eligible participants will be excluded if they meet any of the following criteria: patients with decompensated liver cirrhosis (*1*) complicated by a bone or a joint disorder that might affect the effectiveness of NMES; (*2*) complicated by a fragile skin disease, which might suffer damage due to NMES; (*3*) complicated with a cerebrovascular disorder; (*4*) undergoing hemodialysis; (*5*) complicated by amino acid metabolism abnormalities; (*6*) who are pregnant or lactating; (*7*) participating in other clinical research within 4 months before enrollment; (*8*) complicated by chronic heart disease or using a pacemaker; (*9*) complicated by malignancy other than hepatocellular carcinoma; (*10*) complicated by active infections or tuberculosis; (*11*) complicated by severe hypertension; (*12*) complicated by extreme weakness; (*13*) who will undergo Deceased Donor Living Transplantation; (*14*) who are being included in other trials (all drugs and interventions are permitted during this trial); and (*15*) otherwise deemed inappropriate by the study’s principal investigator.

### Withdrawal criteria

Participants will be withdrawn from this trial after randomization if they meet any of the following criteria: (*1*) if they have requested a withdrawal from the study; (*2*) if it is determined by the investigators that it is inappropriate for the patient to continue participating in the study because of the progression of an underlying disease or a complication or the occurrence of an unknown disease; (*3*) if any adverse event that is ≥ grade 3 of the Common Terminology Criteria for Adverse Events (CTCAE) ver. 4.0 occurs; (*4*) if the patient has been in the intensive care unit for more than 1 month; and (5) if the investigators judge that it is inappropriate for the patient to continue participating in the study for any other reason.

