### Setting and study timeline

All participants will be recruited at Nagasaki University Hospital. Each participant’s information, as listed below, is collected at the prescreening for enrollment (visit 1): age, sex, height, body weight, history, comorbid complications, duration of cirrhosis, and history of cirrhosis treatment. Blood pressure and pulse rate will be measured in a sedentary position at every visit (visits 1–5, and, if withdrawing from the study, at withdrawal). As shown in Table 1, the participants will undergo examinations by blood tests, InBody 770 body composition analysis, and handgrip and quadriceps strength evaluations at enrollment (visit 1) and 1 month (visit 4) and 3 months (visit 5) thereafter. Similarly, they will undergo an examination of quadriceps strength at every visit, except at the start of BCAA (visit 2). When participants need to be withdrawn from the study for any reason, their vital signs will be checked, and they will undergo blood tests within 4 weeks after discontinuing the investigation. Blood specimens are to be obtained at visits 1, 4, and 5.

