**Table 1 Tab1:**
[figure not shown]
The schedule of pre-screening, interventions, and assessments

○ Will be done. A range of ±3 days is allowed for each visit dayThe examination at withdrawal is to be performed within 4 weeks from the date of withdrawal

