### Randomization and allocation concealment

A randomized, open-label, parallel pilot trial design has been set up. On the day on which the study drug is to be firstly administered (visit 2), i.e., after the eligibility assessment, each participant will be sequentially allocated to either the NMES and BCAA group or the control group (NMES only), in a 1:1 ratio, using blocked randomization stratified by age, sex, albumin level, and Child-Pugh score. The allocation will be conducted by the principal investigator using the Internet Data and Information Center for Medical Research (INDICE) system of UMIN.

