### Interventions

#### NMES and BCAA group

Participants allocated to the NMES and BCAA group will undergo NMES within 7 days after LDLT and will be given a BCAA-enriched snack (Aminoleban EN, Otsuka Pharmaceutical Co., Tokyo, Japan; 100 mg/day) after leaving the intensive care unit (ICU) daily for 1 month.

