#### Control group

Participants allocated to the control group will undergo only NMES within 7 days after LDLT for 1 month in addition to their previous treatment.

Both groups will receive muscle stimulation via placement of rectangular electrodes (90 × 50 mm) over the motor points of the quadriceps muscles (~ 5 cm distal to the inguinal fold and 15 cm proximal to the upper border of the patella) bilaterally. The stimulator (Pulsecure-Pro KR-7; OG Giken Co., Tokyo, Japan) delivers biphasic, symmetrical impulses (45 Hz; 400-μs pulse duration; 12 s on and 6 s off; intensity, 40–80 mA). The amplitude is increased to elicit visible muscle contractions and to the maximum level tolerated by the patients. Neuromuscular electrical stimulation sessions in both groups are conducted for 30 min per session, once per day, every weekday over a 4-week period, by a physical therapist, beginning on postoperative day 1 and continuing through postoperative day 30.

During this study, all intervention procedures will be checked by the attending physicians and a transplant coordinator in the Nagasaki University Hospital to improve adherence to intervention protocols.

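### Any grade 3 or higher adverse event, whatever its cause and even after treatment has ended, withdraws a randomised patient from the trial, so the 3-month primary outcome is lost in patients with severe complications

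*Protocol article*

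**What the plan says.** The Withdrawal criteria section opens with "Participants will be withdrawn from this trial after randomization if they meet any of the following criteria". The third criterion applies to any adverse event at or above "grade 3 of the Common Terminology Criteria for Adverse Events (CTCAE) ver. 4.0 occurs". It is mandatory and is not limited to events related to treatment or occurring during treatment. Criteria 2 and 5 add withdrawal at the investigators' judgement, in an open-label trial.

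For a withdrawn patient, Setting and study timeline says that "their vital signs will be checked, and they will undergo blood tests within 4 weeks after discontinuing the investigation". The footnote to Table 1 adds that the "examination at withdrawal is to be performed within 4 weeks from the date of withdrawal". The body of Table 1 is not available in the text reviewed.

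Outcomes defines the primary endpoint as the "difference between the measurement results at baseline (day 0) and 3 months post-LDLT", measured with the InBody 770. Under Interventions, the BCAA snack is given "after leaving the intensive care unit (ICU) daily for 1 month", and NMES runs daily on weekdays, "beginning on postoperative day 1 and continuing through postoperative day 30". The abstract instead gives an intervention period of 3 months.

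Statistical analyses makes the per-protocol set primary and repeats the analysis on the full analysis set (FAS).

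**The concern.** Stopping treatment after a severe event can be justified on safety grounds. Stopping measurement cannot, and this rule does both. It also continues to apply once NMES is over and, for most or all patients, BCAA too. An event then ends follow-up when there is little or nothing left to stop.

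The loss is unlikely to be random. The limitations paragraph of the Discussion says that postoperative complications will influence muscle atrophy, so patients are removed for a reason the authors themselves connect with the outcome. The rule covers every such patient in both arms, so no comparable patients go on to 3-month values from which the missing ones could be estimated.

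Two things are at stake. Power falls in a trial of only 50 patients. The arm difference may also be biased if withdrawal differs between arms, which open-label discretion under criteria 2 and 5 allows. More withdrawal in the BCAA arm would overstate its benefit; more in the control arm would understate it. Even with equal withdrawal, the result describes only patients without severe complications.

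**Working it through.** **Does the rule lose the primary outcome?**

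1. The trigger is any grade 3 or higher event after randomisation, and the consequence is leaving the trial.
2. The text names vital signs and blood tests at withdrawal. Table 1 may also list InBody at that examination.
3. The examination falls within 4 weeks of withdrawal. It supplies a 3-month value only if withdrawal comes late in follow-up. No visible text brings withdrawn patients back for visit 5.
4. NMES ends at day 30, so about 2 of the 3 follow-up months come after it. BCAA runs for 1 month from ICU discharge and so extends into month 2 for some patients.
5. Randomisation takes place on the day study drug is first given, and BCAA starts after the ICU. The criterion of more than 1 month in the ICU therefore matters mainly for readmission.

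**Power.** Inputs from the article: 50 patients, 1:1, two-sided alpha 0.05. No effect size, SD, power or dropout rate is given, so the figure of 50 cannot be reproduced. The table uses a two-sample t-test. The withdrawal proportions are assumptions.

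| Withdrawn in each arm | Evaluable per arm | Detectable difference, 80% power | Power for 0.81 SD |
|---|---|---|---|
| 0% | 25 | 0.81 SD | 80% |
| 20% | 25 × 0.8 = 20 | 0.91 SD | 70% |
| 40% | 25 × 0.6 = 15 | 1.06 SD | 57% |

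A normal approximation agrees closely. Its detectable difference at 25 per arm is (1.96 + 0.84) × √(2/25) = 0.79 SD, and power for that difference is 76%, 71% and 58% at 10%, 20% and 40% withdrawn.

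**Bias.** Let p be the proportion withdrawn in an arm and d the amount, in SD, by which withdrawn patients would fall below completers. The full-arm mean is the completer mean minus p × d, so the completer mean is too high by p × d. The bias in the difference, BCAA minus control, is (p_BCAA − p_control) × d. Taking d = 0.5 to 1.0 as an assumption:

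- Equal withdrawal: 0.
- 20% in one arm, 30% in the other: 0.10 × 0.5 to 0.10 × 1.0 = 0.05 to 0.10 SD.
- 20% in one arm, 40% in the other: 0.20 × 0.5 to 0.20 × 1.0 = 0.10 to 0.20 SD.

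**The case against.** The strongest reply is that the size is entirely assumed. The article gives no rate of grade 3 events and nothing to suggest unequal withdrawal, and CTCAE grading leaves less room for discretion than criteria 2 and 5. Even the largest illustrated bias, 0.20 SD, is well below the detectable 0.81 SD. All of this is right, and it limits what can be said about magnitude. It does not change what the rule does.

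The timing can also be questioned. If the abstract's 3-month intervention is correct, the point about events after treatment largely falls away. The two Interventions subsections agree with each other on about 1 month, and the main point does not depend on this. Severe events during the initial ICU stay may precede randomisation, which would narrow the window for withdrawal but not close it.

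The loss is not total: an event after visit 4 leaves the 1-month data intact, which serves the secondary endpoints but not the primary one. A per-protocol analysis might exclude patients who stopped treatment early even if they were followed. That is a reason to change the analysis set together with the withdrawal rule.

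Finally, the trial is called a pilot, and it lists small size and complications as limitations. Its stated objective is nevertheless to test superiority, so avoidable loss of outcome data matters.

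**Conclusion.** The concern holds and should be fixed. As written, the plan discards the 3-month primary outcome in patients with a grade 3 or higher event, except perhaps when withdrawal falls close to the 3-month visit. The FAS analysis cannot recover values that were never measured.

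The reading of the rule is secure; its numerical effect is not. Under the assumed 20% to 40% withdrawal, power drops by about 10 to 23 percentage points. Bias ranges from none to 0.20 SD, depending on assumed differences between arms and an assumed deficit in withdrawn patients. Confidence is medium because the event rate is unknown.

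**What to change.** Reword criteria 2, 3 and 5 so that they stop the intervention only. Unless consent is withdrawn, keep the InBody 770, strength and ultrasound measurements at the existing 1- and 3-month visits. When treatment stops need not change.

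For the retained data to count, analyse these patients in their allocated arm in the FAS. Make that comparison primary, or at least report it with equal prominence beside the per-protocol result. The FAS also needs rewording: as defined it requires exposure to both NMES and the BCAA snack, which controls never receive. Define it as all randomised patients with a post-baseline muscle measurement.

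The cost is a protocol amendment with review board and registry notice, and a few more completed visits in sicker patients. The downside is some burden on unwell patients and some dilution of the per-protocol effect.

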### Ethical considerations

This protocol was approved by the Clinical Research Review Board of Nagasaki University (CRB7180001), which is certified by Japan’s Ministry of Health, Labor, and Welfare (approval no. CRB19-0015). The study is registered in the Japan Registry of Clinical Trials as jRCTs071190051. The study will be conducted in accordance with the 7th revision of the Declaration of Helsinki 2013 and the Clinical Trials Act enforced in April 2020 in Japan. Any protocol modifications will be communicated to the Clinical Research Review Board at Nagasaki University and registered on the jRCT.

### Setting and study timeline

All participants will be recruited at Nagasaki University Hospital. Each participant’s information, as listed below, is collected at the prescreening for enrollment (visit 1): age, sex, height, body weight, history, comorbid complications, duration of cirrhosis, and history of cirrhosis treatment. Blood pressure and pulse rate will be measured in a sedentary position at every visit (visits 1–5, and, if withdrawing from the study, at withdrawal). As shown in Table 1, the participants will undergo examinations by blood tests, InBody 770 body composition analysis, and handgrip and quadriceps strength evaluations at enrollment (visit 1) and 1 month (visit 4) and 3 months (visit 5) thereafter. Similarly, they will undergo an examination of quadriceps strength at every visit, except at the start of BCAA (visit 2). When participants need to be withdrawn from the study for any reason, their vital signs will be checked, and they will undergo blood tests within 4 weeks after discontinuing the investigation. Blood specimens are to be obtained at visits 1, 4, and 5.

